#### Analysis and archiving

After eCRF data entry is completed, all data have been monitored and raised queries have been resolved, the database will be locked. The complete exported dataset will be transferred to the statistical programmers who will complete the analyses in accordance with the Statistical Analysis Plan. All essential documents and trial data will be held by the sponsor for a minimum of 5 years after the end of the trial. Investigator site files will be archived at the participating sites for 5 years.

#### Data monitoring

The study will be conducted in accordance with the current approved protocol, International Conference of Harmonisation (ICH) Good Clinical Practice (GCP) guidance, relevant regulations and standard operating procedures. Regular monitoring will be performed in accordance with the ICH GCP and a risk-based trial monitoring plan to evaluate compliance with the protocol and accuracy in relation to source documents. In addition, data will be regularly monitored for completeness and quality using automated programmed edit checks. Any data issues are raised as queries in the eCRF system by study monitors.

An independent Data Monitoring Committee (DMC) will monitor data collected during the study for efficacy outcomes and safety. If any issues emerge, the DMC will make recommendations regarding the continuation of the study.

### Statistical analyses

Detailed methodology statistical analyses of study data will be documented in a statistical analysis plan. This trial will be reported according to the CONSORT guidelines for clinical trials.

#### Planned analyses

Analyses will be conducted following intention-to-treat (ITT) principles with outcomes analysed according to the participant’s original, randomised group irrespective of deviations based on non-compliance. The statistician will remain blind to allocation until after the trial is complete and data locked.

All participant baseline data will be summarised descriptively by trial arm. Continuous measures will be reported as means and standard deviations while the categorical data will be reported as counts and percentages.

The primary outcome measure is the percentage of participants defined as study period responders. Where necessary, multiple imputation will be used to impute missing daily abdominal pain and stool consistency scores before the required derived variables are generated (see “Missing data” section below for further details). Once obtained, the primary outcome data will be summarised descriptively and logistic regression will be used to compare the placebo and Enterosgel® groups, with odds ratio and 95% confidence interval reported.

Secondary outcome data will be summarised descriptively at different time points by trial arm. The secondary outcomes will be analysed using either analysis of covariance (ANCOVA) models (for stool consistency and abdominal pain following multiple imputation), linear mixed effects models (continuous secondary outcomes), or mixed effects logistic regression models (binary secondary outcomes). The mixed effects models will contain indicator variables for treatment group and, where appropriate, time plus a time-treatment interaction. The models will be adjusted for the baseline measure of the outcome, where available.

Significance tests will be two-sided at the 5% significance levels unless otherwise stated. All models in the analysis of the double-blind and open-label phases will be adjusted for participant’s age and gender at baseline. Analyses will be undertaken in Stata v13 or later (to be confirmed in the final report).

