#### Exclusion criteria

At screening visit, the participant will not be eligible to proceed if they meet any of the following criteria:
Previously diagnosed coeliac disease (must be confirmed from medical records before randomisation)Previously diagnosed IBD (must be confirmed from medical records before randomisation)Previous bowel cancer or bowel resection (must be confirmed from medical records before randomisation)Other previously known gastrointestinal disorder contributing to the diarrhoea according to principal investigator’s or sub-principal investigator’s evaluation (must be confirmed from medical records before randomisation)Unexplained weight lossUnexplained rectal bleeding (not including a short history of typical haemorrhoidal bleeding in patients aged < 45 years)Previous use of Enterosgel®Use of antidepressant agents, unless used at a stable dose for at least 6 weeksUse of any probiotic supplements, other intestinal adsorbents (activated charcoal, kaoline, diosmectite), slow-release medications or strong opioids (World Health Organisation Step III) (must be confirmed from medical records before randomisation)Participation in any research where treatment is provided, or was provided in the last 3 monthsPregnancy or not willing to use contraception for the duration of the study screening and treatment periods

At baseline visit, the participant will not be eligible to proceed to randomisation if they no longer meet one or more of the criteria above, or if they demonstrated:
Loose stools (Bristol Stool Form Scale (BSFS) 6 or 7) on less than 3 days during the 14 days after screening visit, and/orAverage abdominal pain < 3 during the 14 days after screening visit (scale 0–10: 0 = no pain; 10 = worst possible pain).

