### Outcome measures

#### Primary outcome measure

The primary outcome measure is the percentage of participants defined as responders for abdominal pain *and* stool consistency during at least 4 weeks in the 8-week treatment period, where:
An “abdominal pain intensity weekly responder” is defined as a participant who experiences a decrease in the weekly average abdominal pain score of at least 30% compared with baseline. The weekly average abdominal pain score is derived by scoring the worst pain experienced each day and taking the average for 1 week.ANDA “stool consistency weekly responder” is defined as a participant who experiences a 50% or greater reduction in the number of days per week with at least one stool that has a consistency of BSFS type 6 or 7 compared with baseline.

A participant needs to be a responder for both abdominal pain and stool consistency in the same week to be considered a responder that week.

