### Sample size estimation

The sample size calculation was based on demonstrating superiority for the primary outcome, i.e. response to treatment, with 90% power at 5% significance level. Assuming a response rate of 20% in the placebo group and 35% in the active treatment group, 182 participants per treatment group are required. Assuming 15% drop-out rate, in total 430 participants will need to be enrolled. The response rate of 20% in the placebo group is based on previous studies [31, 32]. The sample size was calculated using a power calculator for binary outcome superiority trial (Sealed Envelope Ltd).

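### The primary logistic model, as written, adjusts for age and gender only; adding the two screening-diary baselines would be an inexpensive improvement, not the repair of an error

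*Protocol article*

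**What the plan says.** All references are to the protocol article; the statistical analysis plan is not available.

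- **Primary model** (Planned analyses): "logistic regression will be used to compare the placebo and Enterosgel® groups, with odds ratio and 95% confidence interval reported". No symptom covariate is named.
- **Covariates for every model** (Planned analyses, last paragraph): age and gender at baseline, for both the double-blind and the open-label phase.
- **Baseline adjustment** (Planned analyses, end of the secondary-outcome paragraph, after the ANCOVA and mixed models): "The models will be adjusted for the baseline measure of the outcome, where available".
- **Responder rule** (Primary outcome measure): a weekly response needs a pain score at least 30% below the participant's baseline and, in the same week, "a 50% or greater reduction in the number of days per week with at least one stool" of type 6 or 7. Study response needs at least 4 such weeks out of 8.
- **Entry floor** (Exclusion criteria): candidates are excluded if they had loose stools "on less than 3 days during the 14 days after screening visit", or a mean pain score below 3. Eligible participants can therefore have 3 to 14 loose-stool days.
- **Data source** (Screening visit): pain and stool consistency are recorded daily for 14 days before randomisation.
- **Allocation** (Randomisation): minimisation, with study centre as the only factor named.
- **Sample size** (Sample size estimation): "Assuming a response rate of 20% in the placebo group and 35% in the active treatment group, 182 participants per treatment group are required". Inflating this for 15% attrition brings the enrolment target to 430.

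**The concern.** The two screening-diary scores are natural covariates for the primary outcome. They are measured before randomisation, they are the yardsticks against which response is judged, and allocation does not balance on them. The plan adjusts the secondary pain and stool outcomes for baseline, but not the primary outcome built from the same two diary items. The sentence that might have brought them in refers to the outcome's own baseline measure, and nobody has a baseline responder status.

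Two things are at stake. If the baselines predict response, leaving them out gives up some precision. A chance difference between arms in baseline severity would also carry through to the estimated odds ratio in that one trial. Neither affects the validity of the test.

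**Working it through.** **1. The plan's own sample size**

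Inputs: 20% v 35%, "response to treatment, with 90% power at 5% significance level" (Sample size estimation); "Significance tests will be two-sided at the 5% significance levels unless otherwise stated" (Planned analyses).

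- Unpooled formula: n = (1.960 + 1.282)² × (0.20 × 0.80 + 0.35 × 0.65) / 0.15² = 180.96, so 181 per group.
- Pooled formula: 185 per group.
- The stated 182 lies between the two. Power at 182 per group is 89.7% (pooled formula).
- Drop-out: 182 / 0.85 = 214.1, so 215 per group and 430 in total, exactly as stated.

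This calculation has no covariates, so the planned power does not rely on baseline adjustment.

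**2. Does the responder rule create dependence on baseline?**

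For the stool half, yes, because days are whole numbers. With k loose days in 14, the baseline is k/2 days per week and a weekly response needs at most k/4 days. At k = 3 the limit is 0.75, so no loose days are allowed. At k = 14 the limit is 3.5, so up to 3 are allowed.

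Assume independent days and no change from baseline. The chance of a weekly stool response is then P(Bin(7, k/14) ≤ floor(k/4)):

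| Baseline loose days of 14 | Chance weekly stool response |
|---|---|
| 3 | 18.5% |
| 4 | 36% |
| 5 | 22% |
| 7 | 6% |
| 8 | 13% |
| 11 or more | 1% or less |

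The trend is downward but jagged: it rises from 3 to 4 and again from 7 to 8. These figures describe one week and the stool half only, not the primary outcome.

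For the full composite (both halves in the same week, at least 4 of 8 weeks), a diary simulation on assumed parameters gave these response rates, from mild to severe baseline bands:

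| Assumed improvement | By baseline pain | By loose-stool days |
|---|---|---|
| Proportional to baseline | 22%, 23%, 26% | 22%, 24%, 26% |
| Absolute amount | 29%, 25%, 18% | 29%, 22%, 19% |

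So neither the strength nor the sign of the dependence is fixed by the definition.

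**3. What adjustment would gain**

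Inputs: 182 per group, marginal rates held at 20% and 35%, one standard-normal baseline score, 4,000 simulated trials per row. The prognostic strength is an assumption, since the article gives none.

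| Odds ratio per SD | AUC | Power without | Power with |
|---|---|---|---|
| 1.0 | 0.50 | 89.8% | 89.8% |
| 1.35 | 0.59 | 90.5% | 90.9% |
| 1.65 | 0.64 | 89.0% | 90.6% |
| 2.2 | 0.71 | 90.3% | 92.9% |
| 2.7 | 0.75 | 89.4% | 93.8% |
| 4.5 | 0.82 | 90.4% | 96.6% |

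Simulated type I error was 4.3% to 5.3%, with or without the covariate. The treatment odds ratio moves from about 2.16 (unadjusted) to between about 2.2 and 2.9 (conditional).

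**4. Size of a chance imbalance**

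With 182 per group, the 95% limit for a chance difference in a standardised baseline is 1.96 × √(2/182) = 0.21 SD. At assumed log-odds slopes of 0.5 to 0.8 per SD, this moves the log odds ratio by about 0.10 to 0.16. The planned effect is ln[(0.35/0.65)/(0.20/0.80)] = 0.77, so the shift is about 13% to 21% of it.

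**The case against.** The case for leaving the plan alone is substantial. Logistic regression with pre-specified age and gender is a valid primary analysis. Omitting a prognostic covariate neither biases a randomised test nor inflates type I error, and about 90% power is reached without these covariates. Any gain is therefore a bonus rather than the recovery of something lost. Randomisation balances baseline in expectation, and the confidence interval already allows for chance imbalance. All of this stands.

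A reader might infer from the responder rule that response depends strongly on baseline severity. The article does not support that. Both criteria are percentage changes, which already scale for severity, and no association is reported. The steep figures in the stool table cover one week and one half of the rule, and part of the contrast is whole-day rounding.

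It can also be said that detail is deferred to a statistical analysis plan. That stands only in part. The article does more than stay silent: it names the primary model, fixes age and gender for all models, and places the baseline rule among the secondary outcomes. If the analysis plan already lists the two baselines, all that remains is to align the article's wording.

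**Conclusion.** The point holds as a suggestion for improvement. The primary model as written contains age and gender but neither screening-diary baseline. The data exist, and adding them needs no larger sample.

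The gain is modest and rests on an assumed association: about 0 to 2 points of power up to an odds ratio of 1.65 per SD, and about 3 to 4 points at 2.2 to 2.7 per SD. The gain of about 6 points appears only at an extreme 4.5 per SD and should not be expected. Adjustment also protects the estimate against a chance baseline imbalance.

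A reader might go further and conclude that the primary analysis is biased, or that the trial is underpowered without these covariates. Neither follows: the simulated error rate is unaffected and the stated sample size reproduces.

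**What to change.** Before unblinding, state the full covariate list of the primary logistic model. Pre-specify baseline mean abdominal pain and baseline loose-stool days from the screening diary, both continuous, alongside age and gender. Consider a flexible form for loose-stool days, because the whole-day rule is not monotone and a straight line may capture only part of it.

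The cost is a change of wording, with no new data and no increase in the 430 to be enrolled. The one downside is that the odds ratio becomes conditional on two more covariates and is less directly comparable with the planned 20% v 35%. A standardised risk difference with its 95% confidence interval, reported beside it, deals with that.

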#### Secondary outcome measures

Secondary outcome measures for the double-blind treatment phase and open-label treatment phase are:
Stool frequency (mean over 8 weeks and the last 4 weeks based on a daily question in the study diary).Stool consistency assessed as average number of days/week with Bristol Stool Scale type > 5 (mean over 8 weeks and the last 4 weeks based on a daily question in study diary, and percentage of responders where responder is defined as a participant with ≥ 50% reduction in this outcome compared with baseline (i.e. screening period)).Abdominal pain (mean over 8 weeks and the last 4 weeks based on a daily question in the study diary, and percentage of responders where responder is defined as a participant with ≥ 30% reduction in abdominal score compared with baseline (i.e. screening period)). Abdominal pain is scored on a scale from 0 to 10, where 0 means no pain at all and 10 means the worst possible pain imaginable.Bloating (mean weekly score over 8 weeks and the last 4 weeks based on a weekly question in study diary). Scale of bloating is from 0 to 6, where 0 means bloating was not bothersome at all and 6 means bloating was greatly bothersome.Urgency (mean weekly score over 8 weeks and the last 4 weeks based on a weekly question in the study diary). Scale of urgency is from 0 to 6, where 0 means no urgency at all and 6 means a very great deal of urgency with bowel movements.Adequate relief of global IBS symptoms (percentage of participants based on a weekly question in study diary).IBS Severity Scoring System (IBS-SSS) score (weekly questionnaire)IBS-related Work Productivity and Activity Impairment (WPAI:IBS; weekly questionnaire to assess percentage work time missed due to IBS, percentage impairment while working due to IBS, percentage overall work impairment due to IBS, percentage activity impairment due to IBS).IBS Quality of Life (IBS-QOL) score (4-weekly questionnaire)Patient Health Questionnaire 12 Somatic Symptom (PHQ-12 SS) scale (4-weekly questionnaire to assess total score and individual symptoms headache (e.), tiredness (n.) and sleep (o.))Use of rescue medication, i.e. loperamide (total number of days loperamide used each week and average over 8 weeks based on a weekly question in study diary)Adverse events (percentage of participants reporting serious adverse event (SAE) and adverse events (AE) possibly related to treatment and total number of SAEs and AEs reported)

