#### Baseline visit (week 0)

After the 14-day screening period, screening diary data will be reviewed to check eligibility against the diary-based eligibility criteria. If an electronic diary was used, the diary system will automatically evaluate eligibility. If a paper diary was used, the site investigators should enter the diary data in the electronic database to allow the system to evaluate eligibility. A negative pregnancy test must also be obtained from any female participants of childbearing potential. Participants whose eligibility is confirmed will complete study questionnaires (IBS-SSS, IBS-QOL, PHQ-12 SS, WPAI:IBS) and be randomised to blinded treatment. Participants will also receive a pack of paper questionnaires (IBS-SSS, IBS-QOL, PHQ-12 SS, WPAI:IBS) to complete at home during the treatment phase. In total, 20 study participants at selected research sites will be selected by the randomisation program for stool sample testing. A separate consent will be sought for the provision of stool samples. The selected participants who consent, will be provided with a stool sample kit and a pre-paid postage envelope to post the sample to the central laboratory where the samples will be analysed. Participants recruited to the main study from pre-selected sites will be invited to take part in MRI assessment. These participants will be provided with a separate MRI information sheet at baseline visit and will have the opportunity to discuss the assessment with the research team and ask any questions before deciding whether they wish to consent to MRI by signing a separate written informed consent form. If a participant decides not to consent to stool sample testing or MRI assessment, this will not affect their participation in the main study. Participants who consent to MRI will undergo two scans: at baseline (although not necessarily on the same day as the baseline visit) and 12 weeks later, i.e. after 4 weeks of open-label treatment. The scans will take place at Newcastle Upon Tyne Hospitals and will not last longer than 20 min involving structural and motility (cine) imaging.

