#### Follow-up visit 2 (week 16)

Participants will complete study questionnaires (IBS-SSS, IBS-QOL, WPAI:IBS, PHQ-12 SS), and AEs and changes in medical history and medications will be reviewed. All participants will be asked the following question (replying (a) yes or (b) no): With regard to your IBS symptoms, compared with the way you felt before you started study treatment, have you, in the past 4 weeks, had adequate relief of your IBS symptoms? Those participants who respond yes will receive a follow-up phone call in 8 weeks. Those who respond no will receive no further follow-up from the research team and will complete the study at this visit.

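### The weekly adequate-relief model is adjusted only for age and gender, although IBS-SSS is collected before randomisation; the comparison is valid but may be less precise than the data allow

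*Protocol article*

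**What the plan says.** The protocol article lists among its secondary outcomes: "Adequate relief of global IBS symptoms (percentage of participants based on a weekly question in study diary"). The wording of the weekly diary item is not printed. The related question at follow-up visit 2 (week 16) is printed, and it asks for relief "compared with the way you felt before you started study treatment".

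Under Planned analyses, this kind of outcome is assigned to "mixed effects logistic regression models (binary secondary outcomes"). The terms are then set out: "The mixed effects models will contain indicator variables for treatment group and, where appropriate, time plus a time-treatment interaction". Two rules on baseline covariates follow. One ties adjustment to the outcome itself: "The models will be adjusted for the baseline measure of the outcome, where available". The other is general: "All models in the analysis of the double-blind and open-label phases will be adjusted for participant’s age and gender at baseline". No substitute is named for an outcome that has no baseline measure.

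On data in hand before allocation, the section on the baseline visit (week 0) states: "Participants whose eligibility is confirmed will complete study questionnaires (IBS-SSS, IBS-QOL, PHQ-12 SS, WPAI:IBS) and be randomised to blinded treatment".

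**The concern.** Adequate relief is a judgement of change since treatment began, so no pre-treatment value can exist. The phrase on availability is therefore never met for this outcome, and its model is left with age and gender. An outcome such as the IBS-SSS score itself is adjusted for its own baseline.

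The protocol thus accepts prognostic adjustment in principle, but ties it to the same variable measured earlier. For the patient-judged global outcome that wording cannot deliver it, although a pre-randomisation severity score is available at no extra burden. What is at stake is the width of the confidence interval and the power for one secondary outcome.

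**Working it through.** **The protocol's own figure.** No sample size is given for adequate relief. The primary-outcome figure supplies the number analysed. With 20% against 35%, two-sided 5% and 90% power:

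n = (1.960 + 1.282)² × (0.20×0.80 + 0.35×0.65) / 0.15² = 10.51 × 0.3875 / 0.0225 ≈ 181 per group, against the stated 182.

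2 × 182 = 364, and 364 / 0.85 = 428.2, so 429 against the stated 430. The figure reproduces, and this point does not touch it.

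**Which covariates the rule yields for weekly adequate relief**

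- Own baseline: none exists.
- Age and gender: included by the general rule.
- Treatment, and time terms where appropriate: included, but not baseline covariates.
- IBS-SSS at week 0: collected, but not named for this model.

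**Size of the possible gain.** The model simulated was of the planned type: random-intercept logistic, 8 weekly binary values, 364 participants, 600 trials per setting. The following are assumptions, not in the document: participant SD 1.8 on the logit scale, intercept −1, log odds ratio 0.62, no dropout, and age and gender left out. r is the correlation of baseline severity with the participant's propensity for relief. SE is the standard error of the treatment log odds ratio.

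| r | SE without severity | SE with severity | Squared SE ratio | Power without → with |
|---|---|---|---|---|
| 0 | 0.216 | 0.216 | 1.00 | 82% → 82% |
| 0.2 | 0.216 | 0.213 | 1.03 | 83% → 84% |
| 0.3 | 0.216 | 0.209 | 1.07 | 81% → 84% |
| 0.4 | 0.217 | 0.203 | 1.14 | 85% → 89% |
| 0.5 | 0.217 | 0.195 | 1.24 | 82% → 90% |

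The treatment estimate was essentially unchanged, so the squared SE ratio can be read as an equivalent increase in participants: 0%, 3%, 7%, 14% and 24%. A separate rerun at r = 0, 0.2, 0.3 and 0.5 gave standard errors within 0.001 of these. With 600 trials a power of 83% has a Monte Carlo error of √(0.83×0.17/600) ≈ 1.5 points, so the standard errors are the firmer guide.

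**Check by hand.** In a random-intercept model the covariate removes r² of the between-participant variance and leaves the within-participant part alone. So SE² ≈ (4/364) × [1.8²(1 − r²) + w].

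- At r = 0: 0.216² × 91 = 4.246. Since 1.8² = 3.24, w = 1.006.
- r = 0.2: (3.110 + 1.006)/91 = 0.0452, SE 0.213, ratio 4.246/4.116 = 1.03.
- r = 0.3: (2.948 + 1.006)/91 = 0.0435, SE 0.208, ratio 4.246/3.954 = 1.07.
- r = 0.5: (2.430 + 1.006)/91 = 0.0378, SE 0.194, ratio 4.246/3.436 = 1.24.

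These agree with the simulation. The formula also shows that the gain would be smaller if participants differed less than the assumed SD of 1.8.

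**The case against.** The strongest reply is that nothing in the protocol is wrong. The rule provides for outcomes without a baseline, it is prespecified and coherent, and a statistical analysis plan that is not shown may name further covariates. That is right as far as error goes: there is no contradiction here. But the point is about a rule that the article states, and an analysis plan that follows it inherits the gap. If the plan already names IBS-SSS, the point is closed.

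A second reply is that adjustment in logistic regression does not narrow the interval. For one binary value per participant this stands. With 364 participants and 20% against 35% relief (rates borrowed from the primary outcome), adding severity raised the SE from 0.243 to 0.251 at r = 0.3 and from 0.243 to 0.267 at r = 0.5. The odds ratio moved from 2.16 to 2.27 and from 2.17 to 2.49. The benefit was in power only: 89.3% to 90.7% and 89.6% to 93.4%. It does not carry over to the planned repeated-measures model, where the SE fell and the estimate hardly moved.

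A third reply is that r may be near zero, because relief is judged against the patient's own earlier state. This stands. At r = 0 nothing is gained, and at 0.2 or less the gain is negligible.

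That the weekly item is worded like the week-16 question is an inference. Relief from treatment would, however, lack a pre-treatment value under any reasonable wording.

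**Conclusion.** The point holds as a suggestion for efficiency, of low severity. As written, the weekly adequate-relief model carries only age and gender as baseline covariates although a baseline severity score exists, and it may lose precision. The loss is equivalent to 0% to about 24% of participants for an assumed r of 0 to 0.5, with the assumed participant SD of 1.8.

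A reader might infer more, and the document does not support it:

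- **That precision is certainly lost.** No association between IBS-SSS and relief is given, so only a range can be stated.
- **That chance imbalance in severity biases the result.** Allocation is randomised, so omitting the covariate neither biases the comparison nor invalidates the test.
- **That the week-16 question needs the same change.** That question decides who receives the follow-up call; the listed outcome is the weekly diary question.
- **That the primary result is affected.** The primary responder analysis and the 430 enrolled are untouched.

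**What to change.** Under Planned analyses, or in the statistical analysis plan, add that the mixed logistic model for weekly adequate relief is also adjusted for baseline IBS-SSS total, alongside age and gender. Fix this before unblinding, since a covariate added later would look chosen from the results.

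The cost is wording and one covariate in one model. The score is already collected before randomisation, so no new data are needed. A few baseline scores may be missing, and their handling should be stated in the same sentence. If severity proves not to be prognostic, nothing is gained; in the simulation at r = 0 nothing was lost either.
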